### Data sources

We will gather data from April 2009 to June 2015 using the following sources.

#### Organisational data

For Hackney practices, we hold detailed records of RHIVA2 trial educational training sessions, post-trial education sessions and participation in the borough-wide audit of HIV care. For Tower Hamlets, we hold data on timing of the introduction of the NIS. For all boroughs, we will seek to obtain any other relevant activities promoting HIV testing in the practices.

#### Clinical data

##### HIV diagnosis data

Borough-specific master case report forms (CRF) containing lists of patients with a positive confirmatory HIV test result will be generated by the lead HIV clinician from the clinical HIV services in each borough. This master CRF will be shared with the study team in an anonymised format as per the RHIVA2 protocol. At Homerton Hospital, Hackney data on newly diagnosed patients have been collected prospectively as outlined in RHIVA2 (continuous data available from 2009). For Tower Hamlets and Newham, new diagnosis data will be collected retrospectively for the same period. Clinical leads will liaise with Public Health England to categorise patients with a positive confirmatory HIV test into newly diagnosed patients and people already known to be HIV positive, and obtain data on patients who had defaulted from care between 12 and 24 months following diagnosis.

##### HIV testing data

In collaboration with the Clinical Effectiveness Group in the Centre for Primary Care and Public Health (QMUL), we will collect anonymised data on HIV testing in primary care, as per RHIVA2 protocol, using remote searches of borough-specific READ codes used for rapid and serology HIV testing.

### Sample size and analysis

#### Sample size

Sample size calculations for the ITS analysis are based on the number of time points available to perform the analysis. Generally, a minimum of 10–12 time points before and after an intervention are required to determine statistical significance of an intervention.^26 27^ Twelve monthly time points are available before the RHIVA2 trial intervention and a minimum of 13 time points for the period thereafter; and 41 monthly time points are available before the RHIVA2 implementation and a minimum of 29 time points thereafter. For Tower Hamlets, 24 monthly time points are available before the introduction of the sexual health NIS and a minimum of 51 time points thereafter.

#### Longitudinal analysis of effectiveness of RHIVA2 implementation programme in Hackney

We will compare testing rates using an ITS regression approach with a mixed Poisson model (or negative binomial model if there is overdispersion) to analyse the effect of interventions. Mixed Poisson regression will allow for the clustered nature of the data, that is, allowing each practice to have a different intercept (baseline HIV testing rate). We will also adjust for practice list size as an offset variable in the analysis. Using this approach, it will be possible to examine whether there is a change in level and/or a change in regression slope following the implementation of the intervention.

We will first examine the impact of the RHIVA2 intervention on combined serology and rapid HIV testing rate in practices that received the RHIVA2 implementation (post-trial setting, comparing testing rates preintervention and postintervention). We will repeat this analysis including practices which did not receive the RHIVA2 intervention during the trial or the further implementation phase, to act as a comparator. This will allow comparison of testing rates in practices postimplementation to their preimplementation rates, also adjusting for continuing trends in practices that did not receive the RHIVA2 implementation. We will also repeat the analysis using Newham practices (which received no intervention) as a further comparator.

The date of intervention will be defined as the date of the first RHIVA2 training session. We will conduct similar analysis to the above, with the endpoint of HIV diagnosis, rather than testing.

To assess sustainability, we will model testing rates in practices that received the RHIVA2 intervention during the trial period, considering an interaction term between time postintervention and whether practices were retrained. This will allow an assessment to be made about whether retraining influences the slope postintervention, that is, the sustainability of the RHIVA2 intervention.

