The RHIVA2 post-trial implementation programme ran from September 2012 to June 2015 and comprised the following three components^16–18^:Additional post-trial HIV testing training (September 2012 to February 2013). This was offered to all Hackney practices at the completion of the RHIVA2 trial and comprised a modification of the RHIVA2 trial intervention whereby practices were encouraged to offer both routine serology and rapid HIV testing in any clinical setting (rather than just rapid testing at practice registration).Updated sexual health LES. From April 2013, the existing LES was replaced with HIV testing payments to practices of between £7 and £10 for every rapid or serology HIV test carried out in any clinical setting, in addition to a payment of £258 for any new diagnosis.General practice-based HIV care audit (October 2012 to March 2013) of missed diagnoses of HIV and safety of coprescribing with antiretroviral medication in Hackney general practices.^22^

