#### Cross-sectional analysis of effectiveness of the RHIVA2 implementation programme in Hackney, a sexual health NIS in Tower Hamlets and usual care in Newham

We will examine the impact of the sexual health NIS on the serology testing rate in all Tower Hamlets practices (comparing testing rates preimplementation and postimplementation). We will repeat this analysis but also including practices in Newham, which received no intervention at any stage, to act as a comparator. The date of intervention will be defined as the date when the sexual health NIS system went live for all practices (April 2011). We will also compare the RHIVA2 implementation in Hackney with the introduction of the sexual health NIS in Tower Hamlets.

We will conduct similar analysis to the above, with the endpoint of HIV diagnosis, rather than testing.

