## Discussion

The MRC Framework for complex interventions^28^ clearly describes the need for implementation studies that test the effectiveness of interventions found to be promising in phase III randomised controlled trials. Successful translation of such interventions into routine care cannot be assumed; trials take place in tightly controlled conditions that aim to limit bias, with selected (often motivated) participants, while implementation programmes (usually) aim much more broadly to include all potential participants.^29^ Trial interventions will often need to be augmented by a distinct implementation package. Their success will be affected by multiple factors including, but not limited to contextual factors such as, differences in setting, population, organisation of healthcare systems, competing initiatives and financial aspects (including availability of incentives). Evaluations of implementation of trials into routine care are frequently not carried out, and if they are, are often poorly reported.^30^ Such evaluations are highly unlikely to involve randomised designs, and are more likely to be observational, including the use of service evaluations. Designs are often constrained by health systems and data availability, but need to be as robust as possible. New reporting guidelines have recently been published that highlight the need for evaluation of implementation and aim to improve their reporting, such that they can be more easily accessed in the literature and serve to guide others in designing the most effective implementation programmes.^29^

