We cannot exclude occurrence of any cluster or crossover effects, although we would expect for this to be minimal given that we detected a more than fourfold increase in HIV testing rates between the RHIVA2 trial intervention and control practices. In contrast to the network structure in Tower Hamlets, Hackney practices, which were randomly allocated to the trial arms, may have informally worked collaboratively through geographical proximity. Due to this potential clustering effect, inference of generalisability of RHIVA2 findings in other boroughs should, therefore, be treated with caution. Furthermore, an audit of new diagnosis and safe coprescribing was also conducted by our team across 31 of the 44 Hackney practices during the implementation phase‚ potentially causing contamination of control practices. However, the number of both trial intervention (n=13) and control (n=15) practices was comparable, suggesting equal exposure to this audit across both arms.^22^ Although public health teams informally collaborate across Northeast London, crossover between boroughs is unlikely given that services are developed and budgeted separately. Our analysis will adjust for any potential contamination using various vertical and horizontal controls both within Hackney, as well as between boroughs using Newham, which has been devoid of any local service HIV promotional intervention, as control.

Moreover, the RHIVA2 trial and post-trial implementation will not be grouped as the same intervention. We will only use the post-trial implementation practices in the main analysis and only consider the trial intervention practices for the assessment of sustainability. Therefore, the sustainability analysis will have to be interpreted with caution with regards to the sustainability of the post-trial intervention, as the intervention in trial conditions might be different to that outside of trial conditions.

We may not be able to account for missing data such as from patients lost to follow-up after diagnosis in general practice, or from rapid testing pilots conducted in a small number of Newham practices during the study period.

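### The main Hackney analysis covers only practices that took up the post-trial training, so it does not estimate the effect of rolling the programme out to the borough

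*Protocol article*

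**What the plan says.** In the Interventions section on Hackney, the protocol article says of the post-trial training: "This was offered to all Hackney practices at the completion of the RHIVA2 trial".

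The section on the longitudinal analysis then sets the main testing analysis "in practices that received the RHIVA2 implementation (post-trial setting, comparing testing rates preintervention and postintervention". The Discussion confirms the restriction: "We will only use the post-trial implementation practices in the main analysis". Time zero follows receipt of training: "The date of intervention will be defined as the date of the first RHIVA2 training session". Hackney practices that were never trained enter a repeat analysis only as a control: "practices which did not receive the RHIVA2 intervention during the trial or the further implementation phase, to act as a comparator". The cost-effectiveness section uses the same untrained practices as its no-intervention reference.

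For Tower Hamlets, the section on the cross-sectional analysis examines the "serology testing rate in all Tower Hamlets practices", with one date for every practice: "The date of intervention will be defined as the date when the sexual health NIS system went live for all practices (April 2011". That section also plans a Hackney against Tower Hamlets comparison but does not restate which Hackney practices enter it. The same approach is to be applied to HIV diagnosis, the other coprimary outcome.

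**The concern.** The first study question, at the end of the Introduction, asks how effective and cost-effective the intervention is once it runs as a clinical service outside research. For a commissioner, that is the effect of offering the programme to a borough, including practices that do not take it up. The Discussion draws the same line: trials enrol selected, often motivated participants, whereas "implementation programmes (usually) aim much more broadly to include all potential participants". Conditioning the main analysis on acceptance of training brings a similar selection back.

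The planned model does not remove it. A random intercept per practice allows for different baseline testing rates, but not for a different response or trend in practices that chose to be trained. Adding untrained Hackney practices or Newham as comparators adjusts for background trend, but the estimate still refers to acceptors.

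Two readings are at stake: the answer to the first question, and the comparison across boroughs, where Tower Hamlets is represented by all its practices.

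**Working it through.** **1. The plan's own time points.** These are inclusive calendar-month counts for the data window April 2009 to June 2015, which has 75 months.

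- Hackney before: April 2009 to August 2012 = 9 + 12 + 12 + 8 = 41. Stated: 41.
- Hackney after, minimum: February 2013 to June 2015 = 11 + 12 + 6 = 29. Stated: 29.
- Tower Hamlets before: April 2009 to March 2011 = 9 + 12 + 3 = 24. Stated: 24.
- Tower Hamlets after: April 2011 to June 2015 = 9 + 12 + 12 + 12 + 6 = 51. Stated: 51.

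All four reproduce. The Tower Hamlets counts add to 75, but the Hackney counts add to only 70. The 41 runs up to the programme's start in September 2012, while the minimum of 29 starts in the last month of the training window. From September 2012 there are 4 + 12 + 12 + 6 = 34 months, which matches the +34 column of Table 1, and 41 + 34 = 75. So the Hackney clock runs from each practice's own training. A practice that was never trained has no post-period as a programme practice.

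**2. Is there non-uptake?** The offer went to all Hackney practices, and a comparator of practices trained in neither phase is planned. The sustainability model also separates former trial practices by whether they were retrained. The number trained after the trial is not stated. The Discussion says that the audit, another component, reached 31 of 44 practices (70%). That is not training uptake and is not used as such here.

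**3. Illustration of size.** Uptake and rate ratios are assumptions, with equal list sizes and baseline rates. With uptake c, rate ratio RR_t in trained practices and RR_u in untrained ones:

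RR_all = c × RR_t + (1 − c) × RR_u; ratio of trained-only to all-practice = RR_t / RR_all.

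For example, at c = 0.7, RR_t = 1.5 and RR_u = 1.0: 0.7 × 1.5 + 0.3 × 1.0 = 1.35, and 1.5 / 1.35 = 1.11.

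| RR_t | RR_u | RR_all (ratio) at 50% uptake | at 70% | at 90% |
|---|---|---|---|---|
| 1.3 | 1.0 | 1.15 (1.13) | 1.21 (1.07) | 1.27 (1.02) |
| 1.5 | 1.0 | 1.25 (1.20) | 1.35 (1.11) | 1.45 (1.03) |
| 2.0 | 1.0 | 1.50 (1.33) | 1.70 (1.18) | 1.90 (1.05) |
| 1.5 | 1.2 | 1.35 (1.11) | 1.41 (1.06) | 1.47 (1.02) |

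At c = 100%, or when RR_u = RR_t, the ratio is 1.

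**4. Partly exposed comparators.** Suppose untrained practices rise by 1.2 because of the payments or the audit. The Hackney-controlled estimate is then 1.5 / 1.2 = 1.25, below the all-practice value of 1.41 at 70% uptake. In that analysis the error runs the other way. Overstatement is therefore clearest in the uncontrolled and Newham-controlled analyses.

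**The case against.** Several points on the other side stand.

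- A reader might infer that Tower Hamlets is analysed regardless of whether practices took part. The documents do not support this. The Interventions section says the computer template was activated in every Tower Hamlets practice on one day, and it records no non-participation. The two sets differ because delivery differed. The contrast is between an uptake-defined set and a whole borough, not between acceptors and a set known to include refusers.
- The Hackney set for the between-borough comparison is inferred from the longitudinal section, the cost-effectiveness section and the Discussion. The cross-sectional section leaves it open.
- Training is one of three components. The testing payments from April 2013 carry no stated training condition, and the audit reached most practices. Untrained practices may thus have been partly exposed.
- Dating each practice from its own first session is a legitimate choice for a roll-out staggered over six months. It is not a flaw in itself.
- Moving every practice into the programme arm would remove the within-Hackney control, which is also the cost-effectiveness reference.

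The planned random intercepts and the Hackney and Newham comparators mitigate baseline differences and shared trends. They do not address selection on response, and none of these points supplies an estimate for all practices offered the programme.

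**Conclusion.** The point holds as a mismatch between the question and the analysis set. The main Hackney analysis answers for practices that accepted training, and no estimate for all practices offered the programme is described. If the same set is carried into the between-borough and cost-effectiveness comparisons, part of any difference between Hackney and Tower Hamlets could come from how the practices were selected.

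It is tempting to conclude that Hackney's effect is overstated and the comparison favours Hackney. That is the likely direction, but the documents do not establish it. Uptake is not given, the gap disappears at full uptake or if untrained practices change equally, and partial exposure pulls the Hackney-controlled estimate down. With untrained practices unchanged, uptake of 50% to 90% and trained rate ratios of 1.3 to 2.0, the trained-only figure exceeds the all-practice one by about 2% to 33%. This range rests wholly on assumed inputs.

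**What to change.** Add to the existing analyses; do not replace them.

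1. Fit an interrupted time series model to all Hackney practices offered the post-trial programme, at minimum all those outside the trial intervention arm. Use a common September 2012 start, model September 2012 to February 2013 as phase-in, and take Newham as control.
2. Use this estimate for the roll-out reading of the first question and for the Hackney, Tower Hamlets and Newham contrasts. Add it to the between-borough cost-effectiveness comparison as a further scenario with Newham as reference.
3. Keep the trained-practice analysis, with practice-specific dates and the within-Hackney comparator, and label it as the effect of training.
4. State in the cross-sectional section which Hackney practices enter, and report training uptake.

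The cost is one further set of model fits on data already planned for all practices, plus a cost-effectiveness scenario with a different reference group. The Hackney effect will probably be smaller.

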### Design

Service evaluation comprising a pragmatic cohort using an interrupted time series (ITS) analysis and cost-effectiveness analysis. The evaluation will examine the longitudinal impact of interventions in Hackney and the comparative cross-sectional impact of interventions in Hackney, Tower Hamlets and Newham. HIV testing and diagnosis data from 1 April 2009 to 30 June 2015 is being collected.

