### Interventions

#### Hackney

The RHIVA2 intervention was first introduced in April 2010 in 20 general practices randomised to the intervention arm of the RHIVA2 trial (table 1). This theory-based intervention^16–18^ is described in detail in Leber *et al*^14^ and consisted of a practice-based educational training session for the primary care team to promote rapid HIV testing at registration, a follow-up meeting with a nominated practice lead nurse, integration of rapid HIV testing with the general practice computer template, and an incentive payment of £10 per rapid HIV test performed. Testing competence was monitored by an external quality assessment. This intervention was offered in addition to an existing national antenatal HIV screening service offered at the practices, and a sexual health LES promoting sexual health screening including HIV case detection (incentive payments of £265 per newly diagnosed patient) introduced in 2006/2007.^19^

**Table 1 T1:** Schedule for enrolment, interventions and assessment of the study

Timepoint	Study period									
	Control period			Practice allocation	Post-allocation			Close-out		
	−41 months	−24 months	−12 months	0 months	+1 months	+2 months	≥12 months	+29 months	+34 months	+51 months
RHIVA2 trial:			X							
Allocation				X						
Intervention					X					
Enrollment						X	X	X		
RHIVA2 post-trial implementation:	X									
Allocation				X						
Intervention					X					
Enrollment						X	X	X	X	
Tower Hamlets:		X								
Allocation				X						
Intervention				X						
Enrollment				X	X	X	X	X	X	X
Assessments:										
HIV testing	X	X	X	X	X	X	X	X	X	X
HIV diagnosis	X	X	X	X	X	X	X	X	X	X

RHIVA2, Rapid HIV Assessment 2.

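### The sustainability model crosses time since first training with a yes/no retraining attribute, so months before retraining help set the slope attributed to retraining

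*Protocol article*

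**What the plan says.** The section on the longitudinal analysis in Hackney restricts the sustainability analysis to the practices that had the intervention in the trial. The term that carries retraining is described in these words: "considering an interaction term between time postintervention and whether practices were retrained". The section also states what will be concluded from that term: "whether retraining influences the slope postintervention, that is, the sustainability of the RHIVA2 intervention".

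The same section fixes the time origin: "The date of intervention will be defined as the date of the first RHIVA2 training session". The Hackney interventions section gives the calendar. For the trial, "The RHIVA2 intervention was first introduced in April 2010 in 20 general practices randomised to the intervention arm". The further training ran from September 2012 to February 2013, and "This was offered to all Hackney practices at the completion of the RHIVA2 trial". The Design section gives the data window: "HIV testing and diagnosis data from 1 April 2009 to 30 June 2015 is being collected".

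The random part of the model is a practice-specific intercept. The article does not say that the retraining variable changes value at the retraining date, that a second change point is fitted, or that time restarts at retraining. The organisational data section says that detailed records of both trial and post-trial sessions are held.

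**The concern.** Whether a practice was retrained reads as one attribute per practice. Time since the intervention cannot mean time since retraining, because practices that were not retrained have no such date. Crossing the two gives each retrained practice a single slope from first training to the end of data, although retraining came more than two years later for a practice trained in April 2010.

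The slope difference between groups then mixes two things: how their slopes differed before anyone was retrained, and what changed afterwards. Retraining was offered and not randomised, so practices that took it up may already have been on a different trajectory. The random intercept absorbs differences in level, not in slope.

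At stake is the article's answer on whether retraining helps to sustain testing, which commissioners, its stated audience, may act on.

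**Working it through.** **1. Reproducing the article's month counts** (inclusive calendar months)
- April 2009 to March 2010: 12, as stated before the trial intervention.
- April 2009 to August 2012: 41, as stated before the implementation.
- February 2013 to June 2015: 29, as the stated minimum after it.
- The minimum of 13 after the trial intervention is matched if the last practice was first trained in August 2011 and the count ends in August 2012. Neither date is given for this count, so August 2011 is an inference.

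**2. Share of post-intervention months that precede retraining**

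Let n be the months from first training to June 2015 and r the months before retraining. The share is r/n.

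| First trained | Retrained | r | n | r/n |
|---|---|---|---|---|
| April 2010 | September 2012 | 29 | 63 | 46% |
| April 2010 | February 2013 | 34 | 63 | 54% |
| August 2011 (inferred) | September 2012 | 13 | 47 | 28% |
| August 2011 (inferred) | February 2013 | 18 | 47 | 38% |

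**3. Dilution of a true slope change**

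Suppose both groups share one slope until retraining, and the retrained group's log rate then gains b per month. With a group main effect in the model, the least-squares interaction is b multiplied by the slope of max(0, t − r) regressed on t, for t = 0, …, n − 1. That multiplier is close to (1 − r/n)² × (1 + 2r/n).
- n = 63, r = 34: approximation (0.460)² × 2.079 = 0.44; exact fit 0.43.
- n = 63, r = 29: exact 0.55.
- n = 47, r = 18: exact 0.66.
- n = 47, r = 13: exact 0.80.

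A true +1.0% per month is therefore estimated as +0.43% to +0.80%. Noise-free Poisson fits over 63 months agree: a true +0.020 in log rate per month gives +0.011 (r = 29) or +0.0085 (r = 34).

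**4. A step read as a slope**

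Suppose retraining raises the rate 1.5-fold at once, with no slope change. The interaction is then ln(1.5) × 6r(n − r) / [n(n² − 1)].
- n = 63, r = 29: 0.4055 × 5916/249984 = 0.0096 per month; exp(12 × 0.0096) = 1.12 per year.
- n = 47, r = 18: 0.4055 × 3132/103776 = 0.0122 per month; exp(12 × 0.0122) = 1.16 per year.

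**5. A persistent prior slope difference** (Poisson fits, n = 63)
- Retrained practices on −0.020 per month throughout, others on −0.010, and no retraining effect: the interaction is −0.010. A model with level and slope-change terms from the retraining month gives a change of 0.000.
- The same prior difference with a true +0.010 change at retraining: the interaction is −0.005 (r = 29) to −0.006 (r = 34), the wrong sign. The time-varying model returns +0.010.

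The slopes and the step in parts 3 to 5 are chosen for illustration. The month counts come from the article, except those that start in August 2011.

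**The case against.** **The text does not say the attribute is fixed.** It is one sentence in a condensed article. Retraining status could be coded month by month, the dates are on record, and an analysis plan that is not shown might do so. This stands as a limit on certainty about the eventual coding. It does not remove the point, because the article names a specific term and the inference to be read from it, and on its plain reading the term does not support the inference. Switching the indicator on at retraining would not be enough either: multiplied by time since first training, without its own level term, it would force a jump at retraining proportional to elapsed time.

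**A reader might infer that falling testing prompted retraining, so that retraining would look harmful.** The article does not support this: the training was offered to all Hackney practices. Uptake may still have been selective, but no trigger is described. Nor should one argue from an earlier decline that stops by itself at retraining. Those data are identical to a prior decline plus a true improvement at retraining, and a time-varying model would credit retraining as well. The sound null case is the persistent slope difference in part 5.

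**The article already urges caution about sustainability.** That caveat, in the Discussion, concerns trial versus non-trial conditions, not the timing of retraining, so it does not answer the point.

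**The magnitudes are illustrative.** This is correct. The section also gives no end date for the sustainability model, so June 2015 is taken from the data window.

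**Conclusion.** On its plain reading, the stated term does not isolate what happened after retraining. Between 46% and 54% of the months behind the retrained slope precede retraining for a practice first trained in April 2010, and 28% to 38% for one first trained in August 2011. True slope changes are diluted, a step is read as a slope, and a pre-existing slope difference is credited to retraining. The direction and size of the net error in the real data cannot be known from the article. The result rests on a constant practice attribute, data to June 2015 and, for the lower range, the inferred August 2011 date.

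A reader might infer that the main results are compromised. They are not: the Discussion says that the main analysis uses only the post-trial implementation practices and that the trial intervention practices serve only to assess sustainability. For that reason this is a point that should be fixed, not one that blocks the plan.

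**What to change.** - Code retraining as 0 until each practice's recorded retraining date. From that date, add a level term and a slope-change term.
- Let the pre-retraining slope differ between trial practices that were and were not retrained.
- Keep never-retrained trial practices as concurrent controls, with a stated reference date so that changes common to both groups are estimated.
- Read the effect of retraining from the post-retraining terms only, and state that uptake was not randomised, so residual confounding remains.

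The cost is revised wording, one recoded covariate and some loss of precision. No new data are needed, since session records are held. The article does not say how many of the 20 trial intervention practices were retrained, so the loss of precision cannot be quantified here.

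### The only term named for assessing sustainability, post-intervention time by retraining, estimates what retraining adds to the slope and not whether the trial effect lasted

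*Protocol article*

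**What the plan says.** The last paragraph of the protocol's section on the longitudinal analysis in Hackney states its aim and its population: "To assess sustainability, we will model testing rates in practices that received the RHIVA2 intervention during the trial period". It names one term for the purpose, "considering an interaction term between time postintervention and whether practices were retrained", and says the result will show "whether retraining influences the slope postintervention, that is, the sustainability of the RHIVA2 intervention".

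Earlier in the same section, the interrupted time series approach is described in general terms: "it will be possible to examine whether there is a change in level and/or a change in regression slope following the implementation of the intervention". That sentence does not say which of these quantities measures sustainability.

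The Discussion confirms the restriction, saying the authors will "only consider the trial intervention practices for the assessment of sustainability". Its one caveat on this analysis is that trial conditions may differ from post-trial conditions. It does not discuss what the interaction measures.

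**The concern.** Sustainability asks whether the rise in testing after trial training persisted. The named interaction asks something else: whether practices trained again had a different slope from those that were not. The two questions can have opposite answers. A gain that disappears at the same rate in every practice leaves the interaction at zero. A gain that persists in full, with retraining adding further growth, makes it non-zero.

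If the interaction is reported as the sustainability result, neither outcome of the test tells a commissioner whether one round of training has a lasting effect. That is the information needed to decide whether repeat training is worth paying for.

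**Working it through.** **Inputs from the protocol**
- Practices: 20 in the trial intervention arm, starting April 2010 (Interventions, Hackney).
- Data window: April 2009 to June 2015 (Design). This gives 12 months before April 2010, matching the Sample size section, and 75 − 12 = 63 months from then on.
- Retraining: September 2012 to February 2013 (Interventions, Hackney). April 2010 to August 2012 is 29 months, the longest follow-up free of retraining.
- Effect size, for scale only: a more than fourfold difference between trial arms (Discussion), used here as a fourfold rise at training.

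The protocol gives no power or precision figure for this analysis, so there is none to reproduce.

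**Algebra**

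For practice i, the segmented model with the named term is

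log rate = a_i + b1·t + b2·post + b3·s + b4·(s × retrained),

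where t is calendar time and s is time since training. The post-intervention trend is b1 + b3 in non-retrained practices and b1 + b3 + b4 in retrained ones. The named term is their difference, b4.

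| Truth | Trend without retraining | b4 |
|---|---|---|
| Gain kept in all practices | 0 | 0 |
| Gain fades equally in all practices | negative | 0 |
| Gain kept, retraining steepens the slope | 0 | above 0 |

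(The trend column takes a flat underlying trend, b1 = 0.) The first two rows have the same b4 although they are opposite answers on sustainability. The first and third have different b4 although the trial effect is equally sustained. This needs no numerical assumptions.

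**Simulation, for scale**

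Assumptions not in the protocol: 10 of 20 practices retrained, list size 6000 and 10 tests per 1000 per year at baseline (6000 × 10/1000/12 = 5 per practice per month), between-practice SD 0.3 on the log scale, all practices trained in April 2010, log-linear decay to zero gain by the last month, Poisson counts, fixed practice intercepts, 200 runs per scenario. The expected trend under complete loss is −ln 4/62 × 12 = −0.268 per year.

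| Scenario | Interaction b4 rejects | Slope change b3 rejects | Total trend b1 + b3: mean per year | Total trend rejects |
|---|---|---|---|---|
| Fourfold gain kept | 6.5% | 4% | 0.000 | 5.5% |
| Fourfold gain lost in all practices | 8.5% | 76% | −0.267 | 100% |
| Gain kept, retraining adds 0.01 per month on the log scale | 100% | 3% | 0.002 | 9% |

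The interaction rejects near the nominal 5% in both of the first two rows. In the third, refitting with retraining coded from September 2012 and a level term included still gave 100% rejection of the retraining slope term.

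Varying the assumed baseline rate changes the power of the slope change b3 against complete loss: 41% at 2 tests per practice per month and 98% at 10. The interaction stayed at 4% and 5%.

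**What the better quantity would show**

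The fitted-to-counterfactual ratio at s months is exp(b2 + b3·s). If the gain is kept, it is 4 at every time. Under complete log-linear loss it is 4^(1 − 12/62) = 3.06 at 12 months and 4^(1 − 24/62) = 2.34 at 24 months.

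**The case against.** The strongest objection is that the interaction is one term in a segmented model that also contains the post-intervention slope. A reader might infer from this point that a vanished effect would go undetected in the planned analysis. The documents do not support that: the protocol says level and slope changes can be examined, and in the simulation the total trend found the loss in every run. The criticism applies to the named interaction only. It stands because the protocol does not name the slope in non-retrained practices as the sustainability result.

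Second, the words after the comma in the quoted sentence may refer only to the post-intervention slope, so that sustainability is the slope and the interaction asks whether retraining modifies it. This is a fair reading. It still leaves the paragraph's announced aim with no named estimate, since only the modification is specified. Slope alone is also incomplete, because persistence depends on level and slope together.

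Third, a reader might infer that any benefit of retraining would be flagged as a sustainability finding. That is too strong. A one-off step gain at retraining moves the interaction if practices are simply classed as retrained or not for the whole period. With retraining coded from its start and given a level term, the slope term rejected near the nominal rate (3% to 7%). Only a true change in slope is picked up under correct coding.

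Fourth, the protocol states no decision rule, so no misreading is written into it, and a condensed article may leave contrasts to an analysis plan. Both are true. The point is not missing detail, however: the article states a specific term for a specific aim, and the two do not match.

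**Conclusion.** The point holds in this form: the protocol sets out to assess sustainability and names only a term that measures the effect of retraining on slope. That term has the same value when the trial effect is kept and when it is lost equally in all practices, so it cannot serve as the sustainability result. The right quantities are available from the same model but are not named.

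The conclusion follows from the algebra. The simulation percentages are illustrative and depend on the assumed baseline rate, number retrained, decay shape and size of the retraining gain. The matter should be corrected, but it affects a supplementary analysis and leaves the coprimary comparisons untouched.

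**What to change.** In the sustainability paragraph of the longitudinal analysis section:

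1. Define sustainability as the post-intervention trend without retraining, together with the ratio of fitted to counterfactual testing rate with 95% CI at fixed times after training. For the main estimate, use all trial-intervention practices up to the start of retraining in September 2012. Twelve months fits the protocol's minimum of 13 post-intervention points. A later time such as 24 months may rest on fewer practices.
2. Treat later months in non-retrained practices as supportive only, because retraining was not randomised and testing payments changed in April 2013.
3. Report the interaction only as the effect of retraining on slope, with retraining coded from its start date and a level term included.
4. Reword the clause that links the interaction to sustainability.

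The cost is a change of wording and a few contrasts from data already being collected. The downside is precision. With 12 pre-intervention months the counterfactual trend is poorly estimated and the ratio will have a wide interval. The simulation shows the direction: the slope change, which depends on the pre-intervention trend, found complete loss in 76% of runs, against 100% for the total trend, which depends on it far less.
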